## Background

1

Advances in medicine and public health, rising standards of living, and improvements in education and nutrition have lengthened the human life span [1], thereby increasing the prevalence of Alzheimer's disease (AD). The prevalence of amnesic mild cognitive impairment (aMCI), a prodromal stage of AD, is 10–20% in adults aged 65 years or above and increases with age [2]. Researchers posit that early identification and intervention may be the key to mitigate dementia and memory impairments. Deficits in episodic memory, including accelerated long-term forgetting (ALF), are one of the earliest detectable cognitive abnormalities in aMCI and AD [3].

ALF refers to abnormal forgetting over hours to weeks despite normal acquisition or encoding [4]. ALF is believed to be mediated by a disruption in memory consolidation, the memory processing stage in which information is transferred from short-term into long-term memory. The locus coeruleus (LC) plays a key role in driving hippocampal synaptic plasticity required for memory consolidation, in which synaptic connections are modified and strengthened to support the rapid formation of memory events [5,6]. A number of studies have documented abnormal LC activity associated with aMCI and AD [[7], [8], [9], [10], [11], [12], [13], [14]], which likely affects the hippocampal synaptic plasticity necessary for memory consolidation. Interventions that target synaptic plasticity could be promising in managing ALF by improving memory consolidation, and consequently ALF in aMCI subjects.

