### Aims

2.1

The objective of current project is to establish the effectiveness of NITESGON in decreasing ALF in individuals with aMCI. Our primary hypothesis is that participants that receive active NITESGON while learning a word association task will perform better on word recall 7 and 28 days after NITESGON in comparison to control groups. In addition, we hypothesize that active NITESGON will significantly increase gamma oscillations within the medial temporal cortex after NITESGON in association with memory performance in individuals with aMCI 7 and 28 days after NITESGON.

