### Study design

2.3

This study is designed as a prospective, double-blind, placebo-controlled, randomized parallel-group study that will be completed at Trinity College Dublin, Ireland. A total of 100 individuals with amnestic mild cognitive impairment (aMCI) based on diagnostic criteria described by the National Institute on Aging and Alzheimer's Association [17] will be recruited from Alzheimer's Ireland. Subject will receive a (real or control) non-invasive transcutaneous electrical stimulation of the greater occipital nerve (NITESGON) procedure. After providing written informed consent, subjects will be assigned to one of four groups. One group will receive active NITESGON, while the three groups will be control groups. One group will receive sham NITESGON (inactive control), while a second group will receive active NITESGON with local anesthesia (active control; local nerve anesthesia group) and a third group will stimulate the C5/C6 nerve (active control; same sensation different nerve). We will include three control groups so that we are able to verify that the effect is real, location specific and cannot be associated to a sensation effect.

We have opted to use a parallel-group design as it is unclear what the carry-over effect and/or wash-out period will be for NITESGON. Subjects will be randomized after screening evaluation and will be assigned to receive one of the four possible types of NITESGON. To eliminate subjective bias, all subjects and the investigator testing the endpoint measures will be blinded to the type of intervention. The researcher who will control the NITESGON device will not be involved in instructing the participant; this will be performed by a second researcher who will be blind to the stimulation protocol. The primary outcome will be change in memory performance as measured by a word association task, measured at baseline (T0), 7 days after NITESGON (T1) and after 28 (T2) days after NITESGON. Secondary outcomes include changes in resting EEG, which will be assessed immediately before and after NITESGON (see Fig. 1 and Table 1).

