### Sample size

2.9

The study is designed to give us adequate power to detect clinically meaningful differences between the groups. We plan to oversample to a target sample size of 25 subjects per group, with an overall sample of 100 subjects, to assure that our power to detect effects is maintained.

Nineteen individuals per group (total n = 76) would offer us a power of 90% to detect the difference between groups using Cohen's d estimation of a medium effect size (0.20). A sample size of 76 would allow us to see a medium effect size, however the trial is longitudinal which could increase its drop-out rate. Although we do not expect attrition to be large, we expect a dropout rate of no more than 20%. Therefore, an overall sample of 100 subjects will assure enough power to accommodate for the expected drop-out rate.

An intention-to-treat and per-protocol analysis will be performed. For the intention-to-treat analysis, the patient must successfully complete T0 and T1 assessments. For missing observations, the LOCF approach will be used. Exclusion from the population will be finalized prior to database lock in a blinded manner.

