### Statistical analysis

2.10

For our calculations, we will use the normal distribution assumption, which we will test using a normal plot and goodness of fit test. If violations are found, non-parametric tests or transformations will be utilized. Variance equivalence will be tested using the F-test. Our protocol is designed to assure sample independence, and adherence will be closely monitored. Before beginning the main statistical analyses, screening variable levels (e.g., age, sex, education, disease onset, mood) across groups will first be considered to assess group equivalence. If the groups are not balanced on any baseline characteristics, these factors will be considered as co-variate in later multivariate regressions.

The efficacy of NITESGON will be assessed on word recall by testing its effect on the mean change over time relative to the control groups. Memory task performance will be analyzed over time at baseline, and 7 and 28 days after NITESGON, and across groups. Statistically, these tests will be single degree-of-freedom interaction contrasts from a general mixed linear model containing both within- and between-subject variance components. All tests will be based on directional hypotheses in favor of improvements due to NITESGON on the behavioral assessment. We expect large behavioral effects based on our previous studies in control and patient populations.

*EEG.* sLORETA statistical contrast maps between pre and post NITESGON will be calculated for the sham and active groups through multiple voxel-by-voxel comparisons in a logarithm of F-ratio [27]. Statistical analysis is based on estimating, via randomization, the empirical probability distribution for the max-statistic under the null hypothesis comparisons [28]. This methodology corrects for multiple testing (i.e., for the collection of tests performed for all voxels and for all frequency bands). Due to the non-parametric nature of the method, its validity does not rely on any assumption of Gaussianity [28]. A comparison will be made between the contrast map for the active and sham group. The significance threshold is based on a permutation test with 5000 permutations. In addition, the statistical contrast map (pre-post) will be correlated with the difference on in memory improvement.

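### LOCF fills a missing day-28 recall score with the day-7 score, so patients lost after day 7 are scored as having forgotten nothing more, in a trial about forgetting

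*Protocol article*

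**What the plan says.** Four statements in the protocol article bear on this.

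- **Missing data (Sample size, 2.9):** "For missing observations, the LOCF approach will be used". No other method is named.
- **Analysis set (same paragraph):** "For the intention-to-treat analysis, the patient must successfully complete T0 and T1 assessments".
- **Primary outcome (Study design, 2.3):** word-association recall, "measured at baseline (T0), 7 days after NITESGON (T1) and after 28 (T2) days after NITESGON".
- **Primary model (Statistical analysis, 2.10):** "single degree-of-freedom interaction contrasts from a general mixed linear model containing both within- and between-subject variance components", with directional tests in favour of NITESGON.

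The objective (Aims, 2.1) is to "establish the effectiveness of NITESGON in decreasing ALF in individuals with aMCI", and the primary hypothesis is that treated participants "will perform better on word recall 7 and 28 days after NITESGON in comparison to control groups". The Background defines the target: "ALF refers to abnormal forgetting over hours to weeks despite normal acquisition or encoding". Sample size allows for dropout of up to 20% and plans 25 patients per group.

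**The concern.** Carrying a score forward assumes that the outcome stays where it was last seen. Here the outcome is memory for a word list and the condition under study is its loss over hours to weeks, an interval that includes day 7 to day 28. The assumption therefore gives the patients with missing data a favourable course: no further loss. Day 28 is one of the two follow-up times in the primary hypothesis, so the filled values enter a primary comparison directly.

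The resulting bias depends on who drops out of which arm and on how much they would have forgotten, neither of which is known at the design stage. With directional tests, a bias towards the active arm raises the false-positive rate, and a bias the other way costs power. The planned mixed model can use patients with a missing visit as they are, so LOCF is not needed to keep them in the analysis.

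**Working it through.** **Which value is filled.** Recall is scheduled at T0, T1 and T2. The intention-to-treat set requires T0 and T1, so only T2 can be missing, and the last observation is always T1. The imputed T1-to-T2 change is exactly 0 words.

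**The plan's own figure.** The stated 76 patients, inflated for 20% dropout, give 76 / (1 − 0.20) = 95, which the planned 100 covers. Twenty percent of an arm of 25 is 5 patients. The sample size is not in question here; 20% serves only as the plan's upper limit for dropout.

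**Bias formula.** In one arm, let p be the share of the analysis set lost after T1 and D the mean number of words those patients would have lost from T1 to T2. LOCF puts their T2 mean D words too high, so the arm mean is too high by p×D. For active (A) against a control (C):

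bias in the day-28 difference = pA×DA − pC×DC.

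T0 and T1 are observed, so a T0-to-T2 or T1-to-T2 contrast carries the same bias.

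**Numbers.** The documents give no words lost and no dropout by arm. All values of D and all splits of dropout below are assumptions.

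| DA | DC | pA | pC | Bias (words) |
|---|---|---|---|---|
| 5 | 5 | 0.20 | 0.08 | 1.00 − 0.40 = +0.60 |
| 5 | 5 | 0.08 | 0.20 | 0.40 − 1.00 = −0.60 |
| 5 | 5 | 0.20 | 0 | 1.00 − 0 = +1.00 |
| 3 | 3 | 0.20 | 0.08 | 0.60 − 0.24 = +0.36 |
| 8 | 8 | 0.20 | 0.08 | 1.60 − 0.64 = +0.96 |
| 5 | 5 | 0.20 | 0.20 | 1.00 − 1.00 = 0 |
| 3 | 5 | 0.20 | 0.20 | 0.60 − 1.00 = −0.40 |
| 5 | 3 | 0.20 | 0.20 | 1.00 − 0.60 = +0.40 |
| 3 | 5 | 0.08 | 0.20 | 0.24 − 1.00 = −0.76 |

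Two readings follow. When forgetting is equal, the arm with more late dropout is favoured. When dropout is equal, the sign is that of DA − DC.

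Within an arm, if dropouts forget like the rest, apparent forgetting from day 7 to day 28 shrinks to (1 − p) of its true value: 95%, 90% and 80% at 5%, 10% and 20% late dropout.

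**Effect on the test.** Simulation of a two-arm comparison by t-test with no true effect: 25 per arm, SD 8, T1–T2 correlation 0.7, 5-word loss in both arms, dropout at random, one-sided 0.05 (all assumed; the article states no significance level).

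- 5 versus 2 late dropouts (active versus control): type I error about 0.08 for the day-28 difference and 0.09 for the T1-to-T2 change.
- 5 versus 0: about 0.11 and 0.14.
- 2 versus 5: about 0.02 for the change, which is conservative.
- Observed data only: about 0.05 throughout.

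**Standard error.** With 5 late dropouts in each arm, the true standard deviation of the LOCF day-28 difference is √(2×8²/25) = 2.26, and the mean estimated standard error is 2.32. The type I error is not inflated.

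**The case against.** The strongest reply is that the damage is limited. The 20% is a ceiling for the whole trial, attrition is not expected to be large, and some of it may fall before T1. There is a single stimulation session, participants are blinded, and the Safety section reports no significant side-effect difference between active and sham. The documents therefore give little reason to expect dropout after day 7 to differ by arm. A bias of +0.6 word needs 5 versus 2 late losses in arms of 25. The words lost between days 7 and 28 are assumed throughout; the Discussion predicts only worse recall at day 7. All of this stands, and it bounds the size of the problem. It does not defend the rule, which fixes the missing outcome at a value that the trial's own premise makes unlikely.

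Four stronger readings are tempting, and the documents do not support them.

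- **Every dropout is scored as not forgetting.** Patients lost before T1 are excluded from the set, not imputed. That is a separate weakness of the entry rule.
- **LOCF shrinks a real effect when dropout is equal.** This holds only if the active arm loses fewer words after day 7. If the benefit is present by day 7 and losses are then equal, the bias is zero; if the benefit narrows, LOCF inflates it. The Background reports η² of .21 at day 7 and .14 at day 28 in older adults. That is a standardised figure from another population, so it is not decisive, but it gives no support to smaller losses in the active arm.
- **The standard error is too small.** It is smaller than one based on observed T2 scores alone, but in the example above it did not understate the variability of the LOCF estimate.
- **The whole primary analysis is compromised.** Imputed T2 values do not enter the day-7 comparison.

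**Conclusion.** The concern holds for patients in the intention-to-treat set who are lost after day 7. For them the plan writes zero further forgetting into a primary time point. Day-28 recall is overstated in each arm with such losses, provided recall falls between day 7 and day 28; that is inferred from the trial's premise and not quantified in the documents. The day-28 difference is biased by pA×DA − pC×DC, in either direction. For an assumed 5-word loss and dropout within the plan's 20% ceiling, this runs from 0 with equal dropout, through ±0.6 word at 20% versus 8%, to ±1.0 word at 20% versus 0%. In the simulated case, one-sided type I error at 20% versus 8% is about 0.08 to 0.09 against a nominal 0.05. The size is modest and conditional. The direction cannot be known beforehand, and the rule gains nothing that the planned model does not already provide.

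**What to change.** 1. Delete the LOCF sentence from Sample size.
2. Fit the "general mixed linear model containing both within- and between-subject variance components" already planned, by REML, to all observed recall scores at T0, T1 and T2. State that this is valid if data are missing at random.
3. Drop the requirement of a completed T1 for the intention-to-treat analysis, so that patients lost before day 7 contribute what was observed.
4. Add one sensitivity analysis for data missing not at random, for example multiple imputation in which dropouts receive a stated decrement from T1 to T2, varied over a range and by arm.

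The number of patients, the visits and trial conduct do not change. The cost is a change of wording, one extra analysis and a slightly wider day-28 interval. In the example with 5 lost per arm, using T2 scores alone would give a standard error of about √(2×8²/20) = 2.53 in place of 2.32; the mixed model recovers part of that gap through the correlation with T1.

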### Statistical analysis

2.10

For our calculations, we will use the normal distribution assumption, which we will test using a normal plot and goodness of fit test. If violations are found, non-parametric tests or transformations will be utilized. Variance equivalence will be tested using the F-test. Our protocol is designed to assure sample independence, and adherence will be closely monitored. Before beginning the main statistical analyses, screening variable levels (e.g., age, sex, education, disease onset, mood) across groups will first be considered to assess group equivalence. If the groups are not balanced on any baseline characteristics, these factors will be considered as co-variate in later multivariate regressions.

The efficacy of NITESGON will be assessed on word recall by testing its effect on the mean change over time relative to the control groups. Memory task performance will be analyzed over time at baseline, and 7 and 28 days after NITESGON, and across groups. Statistically, these tests will be single degree-of-freedom interaction contrasts from a general mixed linear model containing both within- and between-subject variance components. All tests will be based on directional hypotheses in favor of improvements due to NITESGON on the behavioral assessment. We expect large behavioral effects based on our previous studies in control and patient populations.

*EEG.* sLORETA statistical contrast maps between pre and post NITESGON will be calculated for the sham and active groups through multiple voxel-by-voxel comparisons in a logarithm of F-ratio [27]. Statistical analysis is based on estimating, via randomization, the empirical probability distribution for the max-statistic under the null hypothesis comparisons [28]. This methodology corrects for multiple testing (i.e., for the collection of tests performed for all voxels and for all frequency bands). Due to the non-parametric nature of the method, its validity does not rely on any assumption of Gaussianity [28]. A comparison will be made between the contrast map for the active and sham group. The significance threshold is based on a permutation test with 5000 permutations. In addition, the statistical contrast map (pre-post) will be correlated with the difference on in memory improvement.

*TES Adverse events.* A comparison will be conducted between the active and sham group using a one-way ANOVA with stimulation (active NITESGON vs sham NITESGON) as independent variable and adverse events as dependent variable.

*Blinding.* A Chi-square test will be conducted comparing actual stimulation (active NITESGON vs sham NITESGON) versus participants' expected stimulation (active NITESGON vs sham NITESGON).

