### Study procedure

2.5

We will conduct this study as follows:(1)Screening of individuals with aMCI.(2)Randomly assigning aMCI subjects to one of the four NITESGON groups.(3)Administering one session of 1.5-mA active (*n* = 25) or control (*n* = 25 in each of three control group) NITESGON paired with a word-association task; administered by research assistant.(4)Behavioral assessments after each of the three blocks of studying the word associations and neural measures immediately after the last session of Behavioral assessments (T0).(5)Behavioral assessments at seven (T1) and 28 (T2) days after NITESGON.

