#### Secondary outcome measures

2.7.2

(1)Neurophysiology. Rest-state EEG will be collected immediately before and after NITESGON (T0) and will be correlated with the recall of the word-association task 7 (T1) and 28 (T2) days after NITESGON.(2)TES Adverse events*.* We will use the NITESGON exit questionnaire developed by Brunoni et al. [21] to assess potential side-effect (headache, neck pain, scalp pain, tingling, itching, burning sensation, skin redness, sleepiness, trouble concentrating, mood changes) at the end of T0.(3)Blinding. At the end of the experiment (T2), subjects will be asked if they thought they were assigned to the control or active group.(4)Control assessments. We will collect the California Verbal Learning Test II, Delis Kaplan Color Word Interference Test, Beck Depression (BDI) and Anxiety Inventory (BAI), Trial A & B, COWAT and DIGIT Span to verify that the effect obtained cannot be associated due to differences between groups on these control measures. These will be collected during visit 1 before NITESGON (T0), and 28 days after NITESGON (T2).

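### The EEG comparison uses only active and sham, so a gamma difference cannot be attributed to the occipital nerve, and the stated whole-map search tests the medial temporal gamma hypothesis inefficiently

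*Protocol article*

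**What the plan says.** Section 2.1 states a focused EEG hypothesis, that "active NITESGON will significantly increase gamma oscillations within the medial temporal cortex after NITESGON", in association with recall at 7 and 28 days. Section 2.3 explains the three control groups: they are there to show that an effect is real, tied to the stimulation site and not a product of sensation.

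No arm is exempted from EEG. Section 2.7.2 says "Rest-state EEG will be collected immediately before and after NITESGON (T0" and sets no limit by group. Section 2.5 lists, for the whole study, "neural measures immediately after the last session of Behavioral assessments (T0".

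The EEG paragraph of section 2.10 is narrower in arms and wider in search space. Maps are restricted as follows: "sLORETA statistical contrast maps between pre and post NITESGON will be calculated for the sham and active groups". The between-group step is also limited to two arms: "A comparison will be made between the contrast map for the active and sham group". Error control is by "estimating, via randomization, the empirical probability distribution for the max-statistic under the null hypothesis comparisons", which corrects "for the collection of tests performed for all voxels and for all frequency bands", and "The significance threshold is based on a permutation test with 5000 permutations". The pre-post map is then correlated with memory improvement. In that paragraph neither the tests nor the correlation names the medial temporal cortex or the gamma band.

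**The concern.** Two things do not fit together. First, the arms that could show what causes a gamma change are left out of the analysis of that change. Under section 2.6 the sham current is ramped down over 5 s once it reaches 1.5 mA, so active and sham differ in sustained skin sensation as well as in nerve stimulation. Recall, in the same section 2.10, is compared with the control groups in general; EEG is not.

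Second, a hypothesis about one region and one band is tested by a search over every voxel and every band. That search pays a multiplicity price that a single pre-specified measure would not.

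At stake is the mechanistic claim. A positive EEG result would not be specific to the nerve, and a negative one would be hard to read. There is also a smaller question of when the second EEG is taken, because this could bear on the EEG-recall correlation.

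**Working it through.** **1. What each comparison can separate (sections 2.3 and 2.6).**

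| Comparison with active | Difference between the arms | In the EEG plan? |
|---|---|---|
| Sham | Sustained current, hence both nerve stimulation and sustained sensation | Yes |
| Topical anaesthesia, same current and site | Contribution of peripheral nerves in the skin | No |
| C5/C6, same current | Nerve and site, with sensation mimicked | No |

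At 25 per arm (section 2.9), the two omitted arms are 2 x 25 = 50 of 100 participants. Active against sham alone leaves sensation and stimulation of any other nerve as open explanations.

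**2. Cost of the search.** The article gives no power, alpha, effect size, voxel count or band count for EEG, so there is no EEG figure to reproduce. Assumptions: 25 per arm, because both recordings are made at T0; standardised difference d = 0.8; two-sided 5%; M effective independent tests, with M = 1 for a single pre-specified measure.

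Per-test alpha = 1 - 0.95^(1/M). Power is approximately Phi(d x sqrt(25/2) - z), where z is the two-sided critical value at that alpha. For d = 0.8, 0.8 x sqrt(12.5) = 2.83. With M = 1, Phi(2.83 - 1.96) = 81%. The smallest d detectable with 80% power is (z + 0.84) x sqrt(2/25).

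| M | Power, d = 0.8 | Power, d = 1.03 | Detectable d at 80% |
|---|---|---|---|
| 1 | 81% | 95% | 0.79 |
| 10 | 51% | 80% | 1.03 |
| 100 | 26% | 57% | 1.22 |
| 1000 | 11% | 34% | 1.38 |

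The value d = 1.03 is 2 x sqrt(0.21/0.79), from the day 7 recall effect in older adults reported in the Background. It is a recall effect and serves here only as a larger illustrative value. One-sided testing at 25 per arm and d = 0.8 gives about 88%, 60%, 32% and 14%. With 20 per arm, two-sided, the figures are 72%, 39%, 17% and 6%.

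**3. Power of the direct test against all three controls** (25 per arm, two-sided). With Bonferroni alpha 0.05/3, power per contrast is 67% at d = 0.8 and 89% at d = 1.03. Requiring all three contrasts to be significant at 0.05 gives 62% and 89% (simulation with a shared active arm).

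**4. Interval from last stimulation to EEG.** Current runs only during study phases (section 2.6). After the third study phase come a 30 s rest and a test of 16 s per item, limited to items not yet recalled (section 2.7.1). If EEG follows that test, as section 2.5 says, the interval is 30 + 16k seconds for k items tested:

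- k = 10: 190 s = 3.2 min
- k = 45: 750 s = 12.5 min
- k = 50: 830 s = 13.8 min

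The values of k are illustrative, since the article gives no learning data for aMCI. If EEG follows the last stimulation directly, the interval does not depend on k.

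**The case against.** The strongest reply is that a permutation max-statistic controls the family-wise error rate and allows for correlation between voxels and bands. This stands: the test is valid and carries no false-positive problem. Correlation also makes the effective number of tests smaller than the nominal count, and an effect spread over several voxels gives the search more than one chance. A reader might infer that a true gamma effect would probably be missed. The documents do not support that, because they give neither an effect size nor a voxel count. What stands is that a direct test of the stated hypothesis is more efficient.

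It can also be said that the exact region may be defined in an analysis plan not shown, and that the Background already announces a medial temporal gamma association with memory. That is fair for the region's definition. It does not answer the arms point, because the article itself fixes the comparison as active against sham.

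On timing, a reader might see a flat contradiction between sections 2.5 and 2.7.2, or conclude that recording delay alone would produce the EEG-recall correlation. Neither is established. Section 2.5 describes one stimulation session paired with the task, so an EEG after NITESGON can mean after the whole session. Delay confounds the correlation only if resting gamma changes over those minutes, and the article gives no time course.

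**Conclusion.** The concern holds in two parts of unequal strength. The omission of the anaesthesia and C5/C6 arms is plain in the text and needs no assumption: as written, an EEG difference between active and sham cannot be assigned to the greater occipital nerve. The mismatch between a focused hypothesis and a whole-map search is also in the text, but its size is only illustrative. At d = 0.8 it costs about 30 percentage points of power with 10 effective tests (81% to 51%) and 70 with 1000 (81% to 11%), on an assumed effect size, alpha and test count.

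The EEG timing is a point for clarification, with a possible but undemonstrated confounder behind it. EEG is a secondary outcome; recall is compared with the control groups, so the primary analysis is untouched. The change should be made before EEG data are analysed.

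**What to change.** - Make the main EEG test the per-participant pre-to-post change in medial temporal gamma, with region and band limits fixed before any data are seen.
- Compare active with each of the three controls under a stated multiplicity rule.
- Keep the whole-brain, all-band map as exploratory.
- Correlate the per-participant change with T1 and T2 recall, adjusting for arm so that differences between groups do not drive the association.
- State whether the post-stimulation EEG in sections 2.5 and 2.7.2 follows the last stimulation or the last test, and record the interval for each participant so that it can be examined in the correlation.

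The cost is analysis wording, one line on timing and a recorded time. No extra EEG recordings are needed, since no arm is exempted from EEG collection. The price is that the region must be committed to in advance, and that showing specificity against three controls takes more power than one comparison with sham.

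### The active-versus-sham EEG comparison is an unadjusted pre-to-post contrast; using the pre-stimulation EEG as a covariate would be more precise unless the pre-post correlation is very high

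*Protocol article*

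**What the plan says.** Section 2.1 (Aims) states the EEG hypothesis: "active NITESGON will significantly increase gamma oscillations within the medial temporal cortex after NITESGON", in association with later recall. Section 2.7.2 lists neurophysiology as a secondary outcome, with resting EEG taken just before and just after stimulation in the T0 session.

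Section 2.10 fixes the analysis in three steps.
- Within arm: "sLORETA statistical contrast maps between pre and post NITESGON will be calculated for the sham and active groups", voxel by voxel, on the logarithm of an F-ratio.
- Between arms: "A comparison will be made between the contrast map for the active and sham group".
- Error control: a max-statistic approach covering all voxels and all frequency bands. "The significance threshold is based on a permutation test with 5000 permutations".

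No model with pre-stimulation EEG as a covariate is named. The one covariate rule in the section is conditional: "If the groups are not balanced on any baseline characteristics, these factors will be considered as co-variate in later multivariate regressions". Its examples of screening variables are age, sex, education, disease onset and mood, and nothing applies the rule to the EEG maps.

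Section 2.9 (Sample size) sets a "target sample size of 25 subjects per group, with an overall sample of 100 subjects" and does not refer to EEG.

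**The concern.** Allocation is randomised and the first EEG recording precedes stimulation, so resting power before stimulation is a true baseline for the EEG outcome. Comparing pre-to-post contrasts between arms fixes the weight on that baseline at 1. Estimating the weight targets the same arm effect with smaller variance, unless the two recordings are almost perfectly correlated.

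A related conditional point is regression to the mean. If one arm happens to start with higher resting gamma, a contrast with weight 1 subtracts too much from that arm.

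What is at stake is precision for the gamma hypothesis. That comparison has at most 25 participants against 25, and the information needed to sharpen it is already being collected.

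**Working it through.** **Plan's own figures.** The protocol gives no EEG power, SD, effect size or pre-post correlation, so there is no EEG figure to reproduce. The stated 76 participants at 90% power can be recovered as a group-by-time interaction in 4 groups at 3 times, with the 0.20 read as Cohen's f and an assumed correlation of 0.5. The noncentrality is 76 × 3 × 0.20² / (1 − 0.5) = 18.24 on 6 and 144 df, and the power is 0.901. That layout fits the recall outcome; EEG is recorded only twice, both at T0.

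**Inputs for the EEG check.**
- From the protocol: n = 25 per arm; pre and post recordings in one session; log scale; no covariate.
- Assumed: each participant contributes a post-minus-pre log difference (the article does not say exactly how the two maps are compared); equal pre and post variances, with SD 1; rho from 0.5 to 0.9; a true arm difference of 0.4 or 0.6 SD; one test at two-sided 5%.

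**Variances per participant.**
- Contrast: 2(1 − rho).
- Baseline-adjusted: 1 − rho².
- Ratio, adjusted to contrast: (1 − rho²) / [2(1 − rho)] = (1 + rho)/2.
- Estimating the slope multiplies the adjusted variance by about 1 + 1/(2n − 4) = 1 + 1/46 = 47/46.

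**Break-even.** Setting (1 + rho)/2 × 47/46 = 1 gives rho = 92/47 − 1 = 0.957. Above that value adjustment gains nothing at 25 per arm.

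**Power.** This uses the noncentral t with noncentrality delta / sqrt(2v/25), where v is the variance above, on 48 df for the contrast and 47 df for the adjusted model. The slope cost is included. For example, at rho 0.5 and delta 0.6, the contrast has v = 1.00 and noncentrality 2.12. The adjusted model has v = 0.75 × 47/46 = 0.766 and noncentrality 2.42.

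| rho (assumed) | Variance ratio with slope cost | 0.4 SD: contrast → adjusted | 0.6 SD: contrast → adjusted |
|---|---|---|---|
| 0.5 | 0.77 | 28% → 35% | 55% → 66% |
| 0.7 | 0.87 | 43% → 48% | 77% → 82% |
| 0.8 | 0.92 | 59% → 63% | 91% → 93% |
| 0.9 | 0.97 | 87% → 88% | 99.6% → 99.7% |

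From unrounded values, the gains are about 7 to 11 points at rho 0.5, 5 to 6 at 0.7, 2 to 4 at 0.8 and at most 1 at 0.9. In sample-size terms, the gain is worth 25/0.766 ≈ 33 rather than 25 per arm at rho 0.5, and 25/0.868 ≈ 29 at rho 0.7.

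**Chance imbalance.** The difference in baseline means between two arms of 25 has SD sqrt(2/25) = 0.28 SD. A gap above 0.2 SD in either direction has probability 2[1 − Φ(0.2/0.283)] ≈ 48%. Given a gap g, the contrast comparison is shifted by −(1 − rho)g. For g = 0.28 that is −0.14 SD at rho 0.5 and −0.03 SD at rho 0.9.

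**The case against.** The strongest reply is that nothing here is an error. A pre-to-post contrast compared between randomised arms is unbiased over randomisation, and a permutation threshold protects its error rate. A reader might infer that a chance imbalance in resting gamma would produce a false stimulation effect. The documents do not support that as a defect of the test. The shift exists only given an observed imbalance; over randomisation it is part of the contrast's variance, which the permutation distribution reflects. It is the same precision loss seen from another side, not a second problem.

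A reader might also describe the plan as using a raw difference or ignoring the baseline. Neither is right: the scale is a log F-ratio, and the pre-stimulation recording is the reference. If that ratio compares post with pre power, its log is a difference of logs and the weight on baseline is still 1, but the article does not spell this out.

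The objection to the size also stands. Every input except the sample size is assumed. Both recordings fall in one session, so rho may well be high, and at 0.8 to 0.9 little is gained. The single 5% test is a stand-in; the planned threshold spans all voxels and bands, so the percentages are not the power of the planned analysis. EEG is a secondary outcome and did not drive the sample size.

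A full analysis plan, not shown, might add a covariate. That does not answer the point, because the protocol itself states the between-arm method.

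**Conclusion.** The point holds as a modest matter of efficiency on a secondary outcome. The protocol fixes an unadjusted contrast although a usable baseline covariate is recorded, and the adjusted comparison is more precise for any rho below about 0.957 at 25 per arm. Under the stated assumptions the gain runs from about 11 power points (rho 0.5, 0.6 SD) to almost nothing (rho 0.9). The documents do not show where in that range the trial lies. They do not support a claim of bias, inflated type I error or an invalid test. The change is worth making because it is nearly free.

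**What to change.** In the EEG paragraph of section 2.10, specify the between-arm comparison as post-NITESGON log power modelled on arm, with the same participant's pre-NITESGON log power at the same voxel and frequency band as covariate. Keep the max-statistic correction with 5000 permutations, for example by permuting covariate-adjusted residuals. Keep the whole-brain, all-band scope; the within-arm pre-to-post maps can still be shown. A prespecified medial temporal gamma region is optional and is not needed for this change. Write it in before unblinding.

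The cost is one degree of freedom and a short script. No new data, visits or participants are needed.
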